### Intervention Method

#### Overview

All participants receive standardized patient education and consultation regarding lifestyle, diet, and disease management throughout the study period.

On this basis, participants in the intervention arm receive active WW-1 granules, whereas the control arm receives visually identical placebo preparations. Both formulations were produced by Hunan Xinhui Pharmaceutical Co., Ltd. (Hunan, China) and authenticated using HPLC-MS analysis. The matched placebo replicates the active drug in all sensory characteristics (color, aroma, and flavor) and packaging. To maintain strict blinding integrity against the distinct sensory characteristics of the herbal formula, the placebo granules were formulated with a subtherapeutic dose (5%) of the WW-1, combined with matching pharmaceutical excipients. This 5% concentration aligns with the technical guidelines for TCM clinical trials issued by the National Medical Products Administration of China, providing necessary sensory fidelity without exerting any pharmacological therapeutic effect.

Both groups follow an identical administration regimen: oral intake of 1 sachet twice daily for 24 weeks. No additional pharmacological treatments for CAG are permitted during the trial. The overall timeline of this double-blind study, including treatment allocation and evaluation points, is presented in Table 1.

**Table 1 table1:** Schedule of the multicenter, randomized, double-blind, placebo-controlled clinical trial.

Stage procedure	Screening period	Washout period	Treatment period						
	Visit 1 (–14 d ~ 0 d)	1 week	Visit 2 (0 day)	Visit 3 (4 weeks)	Visit 4 (8 weeks)	Visit 5 (12 weeks)	Visit 6 (16 weeks)	Visit 7 (20 weeks)	Visit 8 (24 weeks)
Screening for inclusion/exclusion	✔								
Sign informed consent form	✔								
Demographic data	✔								
Disease risk factors	✔								
Past medical history	✔								
Medical comorbidities and current medication	✔			✔	✔	✔	✔	✔	✔
C13/C14 urea breath test	✔								
Gastroscopy and pathology	✔								✔
Tongue coating, saliva, stomach and fecal microbiota collection	✔								✔
TCM^a^ syndrome scoring			✔	✔	✔	✔	✔	✔	✔
Vital signs	✔		✔	✔	✔	✔	✔	✔	✔
Blood routine	✔								✔
Urine routine	✔								✔
Stool routine and occult blood	✔								✔
Liver function tests (AST^b^ and ALT^c^)	✔								✔
Renal function tests (BUN^d^ and Cr^e^)	✔								✔
Electrocardiogram	✔								✔
Adverse events				✔	✔	✔	✔	✔	✔
Dispensing medication			✔	✔	✔	✔	✔	✔	

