### Outcome Evaluation

The primary outcome, OLGA improvement, is evaluated based on assessments at baseline (visit 1) and posttreatment (visit 8). The severity of gastric atrophy is assessed at baseline and post-treatment according to the OLGA staging system, with the overall stage at each time point determined by the most severe atrophic grade across all biopsy sites. Patients are categorized into three groups based on changes in OLGA stage: regression, defined as a reduction of ≥1 stage after treatment; stable, defined as no change in OLGA stage after treatment; and progression, defined as an increase of ≥1 stage after treatment.

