Secondary outcomes include the improvement of gastric mucosal atrophy and IM (assessed at visits 1 and 8), as well as changes in TCM syndrome scores (assessed at visits 1, 2, 3, 4, 5, 6, 7, and 8). Based on the histopathological characteristics of CAG, a graded scoring system will be used for the pathological assessment. The severity of gastric mucosal atrophy and IM will be classified into 4 grades—absent, mild, moderate, and severe—which will be assigned scores of 0, 2, 4, and 6, respectively. In cases where multiple biopsy specimens or histological sections from a single patient exhibit varying degrees of lesions, the score corresponding to the most severe lesion will be assigned. The improvement in these pathological scores from baseline to posttreatment will be compared between the 2 groups. Additionally, clinical symptoms will be quantitatively evaluated using a standardized scoring method. The primary symptoms include stomach pain and fullness, while secondary symptoms encompass gastric discomfort, poor appetite, dry mouth, bitter taste in the mouth, belching, acid reflux, heartburn, and fatigue. The symptom grading criteria are formulated according to the *Guiding Principles for Clinical Research of New Traditional Chinese Medicines* (2002 edition). Specifically, primary symptoms will be comprehensively assessed based on their severity and frequency, and categorized into 4 grades (absent, mild, moderate, and severe), scoring 0, 2, 4, and 6 points, respectively. Secondary symptoms will be evaluated using the same 4-tier scale but will be scored as 0, 1, 2, and 3 points, respectively. The total symptom scores will be recorded at baseline and at 4-week intervals throughout the treatment period. Changes in the total symptom scores relative to baseline will be compared between the 2 groups to comprehensively assess symptom improvement.

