### Statistical Analysis Plan

The approach of this study is to use an intention-to-treat analysis, ensuring that all participants are included in the analysis as originally assigned. Specialized statisticians will handle the statistical analysis in a blinded manner to maintain the integrity of the results. Regarding missing data, particularly for the primary histopathological end point, we will address this issue using the Last Observation Carried Forward method to impute missing data. This approach will help mitigate the potential bias introduced by incomplete data and ensure that the analysis remains robust. Using SAS software (version 6.12; SAS Institute Inc.), all statistical tests will be 2-sided, with a *P* value of ≤.05 considered to indicate statistical significance. Initially, we will assess the baseline balance to determine the comparability of the intervention and control groups in terms of their fundamental characteristics. For quantitative data, we will provide a comprehensive description including the count, mean, SD, median, and range (minimum-maximum), and use either a *t* test or a Wilcoxon rank sum test to compare the 2 groups. Qualitative data will be presented in terms of frequency and percentage, with a chi-square test or Fisher exact test used to evaluate differences between the groups. In the analysis of combined medication use, we will enumerate the number and percentage of occurrences and then apply a chi-square test or Fisher exact test to analyze any disparities between the groups. For the assessment of treatment compliance, we will enumerate the cases where the administered dosage of the experimental drug falls below 80%, exceeds 120%, or lies within the 80%-120% range and subsequently perform a chi-square test or Fisher exact test to identify any significant differences.

Regarding safety analysis, we will detail the incidence of AEs and serious AEs that occur during the treatment period. We will also present detailed tables outlining the specifics of AEs and serious AEs to provide a thorough understanding of the safety profile of the treatment.

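### The symptom-score baseline differs between the outcome text and Table 1, and the stated unadjusted test on change from baseline gives up precision that baseline adjustment would recover

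*Protocol article*

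**What the plan says.** The Outcome Evaluation section lists, as a secondary outcome, "changes in TCM syndrome scores (assessed at visits 1, 2, 3, 4, 5, 6, 7, and 8". Later in the same paragraph it says: "The total symptom scores will be recorded at baseline and at 4-week intervals throughout the treatment period". It then gives the comparison: "Changes in the total symptom scores relative to baseline will be compared between the 2 groups to comprehensively assess symptom improvement". It names no visit for that comparison.

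In Table 1 (Intervention Method, Overview) the row "TCM^a^ syndrome scoring" is blank at visit 1 and at the 1-week washout, and is ticked at visits 2 to 8, that is, day 0 and weeks 4, 8, 12, 16, 20 and 24.

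For the primary histology outcome the article ties baseline to visit 1: it "is evaluated based on assessments at baseline (visit 1) and posttreatment (visit 8". No sentence ties the symptom baseline to a visit number.

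For quantitative data the Statistical Analysis Plan section will "use either a *t* test or a Wilcoxon rank sum test to compare the 2 groups", and "all statistical tests will be 2-sided, with a *P* value of ≤.05 considered to indicate statistical significance". Last observation carried forward is the stated remedy for missing data, with emphasis on, but not restriction to, the primary endpoint. Randomisation is stratified by centre and baseline OLGA/OLGIM stage (Randomization, Allocation, and Blinding).

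**The concern.** There are two linked problems.

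First, a change score needs a defined starting value. The outcome text implies two pre-treatment symptom scores (visits 1 and 2) and Table 1 implies one (visit 2). A site following the text and a site following the table would collect different data, and the analyst would have to choose the baseline afterwards. Because the article uses visit 1 as baseline for the primary outcome, a reader could carry that over to a visit at which Table 1 schedules no symptom score.

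Second, the symptom score is measured before treatment and six times afterwards, but the stated test uses the baseline only by subtraction. It ignores the stratification factors and makes no joint use of the repeated visits. With 55 participants per arm, which the article itself describes as relatively small, that discards precision available from data already being collected.

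**Working it through.** **The plan's own figure.** No figure is given for the symptom score. The only stated calculation is the sample size, and it reproduces. With n = (1.96 + 0.84)² × [π1(1−π1) + π2(1−π2)] / (π1 − π2 − 0.10)², using unrounded normal quantiles (squared sum 7.849):

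- OLGA: 7.849 × 0.3375 / 0.0625 = 42.4, so 43 per arm; 43/0.8 gives 54.
- OLGIM: 7.849 × 0.3172 / 0.0576 = 43.2, so 44 per arm; 44/0.8 = 55.

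The total of 110 rests on histology alone, so nothing below changes it.

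**Visit schedule, side by side.**

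| Source | Symptom score at visit 1 | Symptom score at visits 2–8 |
|---|---|---|
| Outcome Evaluation, visit list | yes | yes |
| Table 1 | no | yes |
| Outcome Evaluation, baseline plus 4-weekly wording | not stated | fits day 0, then weeks 4 to 24 |

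The blank at visit 1 does not look like a text-extraction fault. The vital-signs row of the same table keeps its visit 1 tick and has eight ticks, matching the visit list in the Safety Outcome section. That list is identical to the one given for symptom scores, so the latter may be a drafting slip.

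**Precision.** Assume a common variance of 1 and a correlation r between baseline and follow-up score.

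- Variance of the change score: 2(1−r).
- Residual variance after baseline adjustment: 1−r².
- Ratio: (1−r²) / [2(1−r)] = (1+r)/2, which is below 1 for every r below 1.

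The documents give no r, so a range is shown. The third column is the number per arm that an unadjusted change analysis would need to match 55 per arm with ANCOVA (55 divided by the ratio). The last column is the ANCOVA power for an effect that the unadjusted change test detects with 80% power.

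| Assumed r | Variance ratio | Equivalent n per arm | Power with ANCOVA |
|---|---|---|---|
| 0.3 | 0.65 | 85 | 93.5% |
| 0.5 | 0.75 | 73 | 90% |
| 0.7 | 0.85 | 65 | 86% |
| 0.9 | 0.95 | 58 | not calculated |

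The formula applies to the t test; it does not carry over directly to the Wilcoxon option.

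**If every visit were tested.** Six post-baseline visits at 5% would give 1 − 0.95⁶ = 26.5% if the tests were independent. They cannot be: with equally correlated visits, two changes from one shared baseline have covariance 1−r and variance 2(1−r), hence correlation 0.5 whatever r is. Simulating six t tests under no effect (20,000 trials per setting, 44 and 55 per arm, compound-symmetry and first-order autoregressive correlation with r from 0.3 to 0.7) gave 17.8% to 20.9%.

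**The case against.** The strongest reply is that little here is an error. An unadjusted change comparison is valid in a randomised trial, the outcome is secondary, and the gain depends on correlations that the documents do not give. The t/Wilcoxon sentence also follows the one on baseline balance, and no sentence assigns it expressly to symptom change. The first three points stand and limit the size of the finding. The last has some force, but the sentence is worded for quantitative data in general and is the only method the article gives for a continuous clinical outcome. It is therefore fair to read it as the stated choice.

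A reader might infer that six tests at 5% are planned. The article does not say so: it says changes will be compared, without naming visits. The wording leaves visit-by-visit testing open, no more, and a full analysis plan may close it.

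A reader might also infer that a visit 1 baseline would bias the result by mixing washout change into treatment change. The comparison is between randomised arms, and washout precedes treatment in both. It would add noise and shift the change within each arm, but would not bias the difference between arms.

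**Conclusion.** The point holds in a limited form. The visit list in the text and Table 1 contradict each other on whether symptoms are scored at visit 1, which leaves the symptom baseline ambiguous. Table 1 and the 4-weekly wording favour visit 2.

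The stated test is valid but inefficient. Under equal variances, baseline adjustment would cut the variance by 15% to 35% for assumed r between 0.7 and 0.3, and by only 5% at r = 0.9. The direction is certain for any r below 1; the size is an assumption.

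The stronger reading, that false positives will rise to 26%, is not supported. The protocol does not commit to six tests, and if it ran all six and claimed any one of them, the chance would be about 18% to 21% under the correlations simulated. The primary outcome and the sample size are untouched.

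**What to change.** 1. Make visit 2 (day 0) the symptom baseline and correct the visit list in Outcome Evaluation to match Table 1. If some sites have already scored symptoms at visit 1, keep those scores as descriptive data.
2. Name the week 24 difference in total symptom score as the single secondary symptom contrast. Report the other visits descriptively with confidence intervals.
3. Analyse that contrast by ANCOVA, or by a mixed model for repeated measures fitted to the observed visits in place of last observation carried forward. Adjust for baseline score, centre and baseline OLGA/OLGIM stage. Either model is acceptable. The mixed model avoids carrying early scores to week 24 for participants who leave; at the planned 20% dropout that is about 0.20 × 55 = 11 per arm.

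The cost is a wording correction and routine programming, with no extra data or participants. Enrollment was still under way when the article was submitted, so the change can be made and dated before unblinding.

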### Safety Outcome

Vital signs examination, including temperature, respiration, heart rate, and blood pressure, is recorded at baseline and posttreatment (visits 1, 2, 3, 4, 5, 6, 7, and 8). The routine blood, urine, and stool tests, liver function tests (alanine aminotransferase and aspartate aminotransferase), and renal function tests (blood urea nitrogen and creatinine) are recorded at baseline (visit 1) and at the end of treatment (visit 8). Throughout the study, adverse events (AEs) will be continuously monitored and documented following treatment administration. Any participant exhibiting abnormalities post treatment—despite baseline normalcy—will undergo periodic assessments until values stabilize. All AEs will be actively tracked until complete resolution is achieved for each participant.

### Mechanism Investigation

To clarify the mechanism of WW-1 in treating patients with CAG, gastric mucosa, saliva, tongue coating, and stool are collected at baseline (visit 1) and at the end of the treatment (visit 8), followed by the Infinium MethylationEPIC BeadChip assay and metagenomic analysis. All sample collection, storage, and transportation processes are carried out in accordance with the standard operating procedure, which has been developed by the expert committee.

### Quality Control of Pathological Blind

Pathological histology is the gold standard for diagnosing CAG. However, consistency among pathologists in clinical practice is often inadequate, particularly in the assessment of atrophy. High-quality international studies related to CAG emphasize the necessity of multiple pathologists’ diagnoses. This study uses a centralized blind pathology approach, using a remote pathology consultation platform for the diagnosis and evaluation of CAG. Pathology experts from the pathology departments of Wangjing Hospital of the China Academy of Chinese Medical Sciences, the Cleveland Clinic in the United States, and Peking Union Medical College Hospital conduct blind diagnoses and reach a consensus. This process ensures the accuracy of pathological results before and after treatment, thereby enhancing the objectivity, rigor, and authenticity of efficacy assessments.

### Quality Control of the Trial

Prior to the trial, all study personnel received protocol-specific training. Investigators must accurately complete CRFs as unalterable primary records, with original laboratory/imaging reports attached. Clinically significant abnormal data require physician verification. Monitors conduct regular site visits, perform source data verification, and provide feedback through reports and meetings to ensure data quality.

To ensure data accuracy, investigators at all participating sites must complete the CRFs with complete honesty. Regular audits are conducted by monitoring personnel to verify the recorded information. When making corrections, the original entries must remain legible, with all modifications accompanied by the investigator’s signature and the date of amendment.

Once reviewed by the monitors, the CRFs are forwarded to the clinical trial data management team. The entire process—including communication between researchers, monitors, and data administrators—is meticulously documented. Prior to data entry, the administrators perform another round of validation. Any discrepancies or clarifications will be recorded as query forms and archived for future review. This structured approach ensures traceability and maintains the integrity of the clinical trial data throughout the study.

### Data Management

Within the drug clinical trial facilities of DHABUCM, the data management software EpiData (version 3.1; EpiData Association) is used, and a database is set up. Data entry personnel carry out independent double data entry. Once the data entry process is completed, a number of CRFs are sampled to assess the entry quality, and any existing issues are addressed. The database is reviewed by data administrators in collaboration with principal researchers. The original CRFs are filed and saved after data entry and verification as required. Electronic data files containing data banks, inspection procedures, analysis results, codebooks, and description files have several backups and are saved on different record media properly. All original files are saved according to “China’s Drug Clinical Trial Quality Management Standard” within the specified time.

### Statistical Analysis Plan

The approach of this study is to use an intention-to-treat analysis, ensuring that all participants are included in the analysis as originally assigned. Specialized statisticians will handle the statistical analysis in a blinded manner to maintain the integrity of the results. Regarding missing data, particularly for the primary histopathological end point, we will address this issue using the Last Observation Carried Forward method to impute missing data. This approach will help mitigate the potential bias introduced by incomplete data and ensure that the analysis remains robust. Using SAS software (version 6.12; SAS Institute Inc.), all statistical tests will be 2-sided, with a *P* value of ≤.05 considered to indicate statistical significance. Initially, we will assess the baseline balance to determine the comparability of the intervention and control groups in terms of their fundamental characteristics. For quantitative data, we will provide a comprehensive description including the count, mean, SD, median, and range (minimum-maximum), and use either a *t* test or a Wilcoxon rank sum test to compare the 2 groups. Qualitative data will be presented in terms of frequency and percentage, with a chi-square test or Fisher exact test used to evaluate differences between the groups. In the analysis of combined medication use, we will enumerate the number and percentage of occurrences and then apply a chi-square test or Fisher exact test to analyze any disparities between the groups. For the assessment of treatment compliance, we will enumerate the cases where the administered dosage of the experimental drug falls below 80%, exceeds 120%, or lies within the 80%-120% range and subsequently perform a chi-square test or Fisher exact test to identify any significant differences.

Regarding safety analysis, we will detail the incidence of AEs and serious AEs that occur during the treatment period. We will also present detailed tables outlining the specifics of AEs and serious AEs to provide a thorough understanding of the safety profile of the treatment.

For the high-dimensional and compositional microbiome data, we will adopt a genome-specific and interaction-focused analytical framework. Briefly, high-quality metagenome-assembled genomes will be reconstructed, and global shifts in the gut microbiota structure will be evaluated using permutational multivariate analysis of variance with permutations. Rather than relying solely on traditional differential abundance testing, coabundance networks will be constructed using Fastspar to account for complex microbial interactions. Subsequently, connected components clustering and weighted correlation network analysis will be applied to identify stably correlated genome clusters, or guilds [14].

### Ethical Considerations

This study adheres to the ethical standards described in the Declaration of Helsinki and relevant Chinese clinical research norms and regulations. The trial protocol has been formally reviewed and approved by the Ethics Committee of Wangjing Hospital, China Academy of Chinese Medical Sciences (approval WJEC-KT2024-022-P002, April 2, 2024). Written informed consent must be obtained from each participant prior to enrollment and randomization. Furthermore, strict measures are implemented to maintain the privacy and confidentiality of all research participants; personal identifying information is fully anonymized, and all participant data are securely stored and accessible only to authorized study personnel.

## Results

The funding began in November 2023. The study was officially initiated on April 20, 2025, with the enrollment of the first participant. This commencement followed the completion of essential preparatory measures, including the formulation of the study protocol, the registration of the clinical trial, the ethical review, and the establishment of the framework for participant recruitment. The study is projected to conclude in October 2026, following the completion of 24 weeks of treatment. The final study results, including efficacy outcomes, safety profiles, and mechanistic insights, are expected to be released after comprehensive data analysis and verification.

